We developed a mortality risk indicator to exclude patients who may not benefit from screening. Existing risk indicators included variables such as insurance type that may differentially exclude patients who are already underrepresented in screening but still might benefit. [33,34] Our model uses predictive factors related to end-of-life risk, from domains similar to those represented in the Epic End of Life (EOL) Care Index, with the Medicaid predictor removed, and additional medication, diagnosis, and utilization variables added (Supplement Table 3). This 3-year mortality prediction model was trained on a cohort of 42,451 patients eligible for CRC screening as of 12/1/17, 12/1/18, and 12/1/19 (three years, used to mimic the length of the intervention) using weighted logistic regression with L1 regularization and 5-fold cross validation, which was implemented via LogisticRegressionCV from the scikit-learn library (v1.0.2) in Python. [35] Of this cohort, 779 (1.8 %) patients were deceased within 3 years. The AUC of this prediction model was 0.844 in the held-out test set, performing similarly to the Epic EOL model (0.838). Using a threshold of 0.9, the model’s accuracy was 97.2 % with a positive predictive value of 26.8 %. Upon completion of enrollment, 625 patients of 19,969 eligible patients (3.1 %) were excluded because of an increased risk for mortality within three years.

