### Randomization

2.3.

In each of four batches, 5000 eligible patients were randomly selected from the approximately 20,000 eligible patients identified. Patients were individually randomized, stratified by practice, to three arms related to outreach in a 1:2:2 ratio to no outreach (arm 1), colonoscopy only (arm 2), or sequential choice of colonoscopy then FIT (arm 3). In the outreach arms 2 and 3, patients were additionally randomized to receive either (a) no additional intervention, or (b) a visit-based, clinician-directed nudge facilitated by the EHR and follow-up text messaging (Fig. 1). Upon completion of enrollment, 19,344 patients were randomized as follows: arm 1 (no outreach): 3877; arm 2a (colonoscopy only, no nudge): 3865; arm 2b (colonoscopy + visit nudge): 3870; arm 3a (sequential choice): 3867; arm 3b (sequential choice + visit nudge): 3865. See Table 1 for participant characteristics by study arm. Randomization was implemented using block randomization with stratification using Way to Health (W2H), an NIH-funded software platform that automates research and outreach for patient engagement. [36]

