Patients randomized to a visit-based nudge arm (2B or 3B) who attend a visit with their PCP additionally receive a visit-based, clinician-directed nudge and a follow-up text 3 days post-visit. The nudges include an EHR static highlighted notification (Epic storyboard banner)(Fig. 2) notifying clinical staff (medical assistants, PCPs, and nursing staff) that a colonoscopy and/or FIT order has been placed on their behalf and encouraging discussion around completion. Patients receive a follow-up text message 3 days after the visit reminding them to follow through on active CRC screening orders (colonoscopy, FIT, or both).

Participants randomized to arm 1 (usual care) do not receive any direct outreach or visit-based nudges from this trial. Fig. 1 summarizes the trial design.

As per usual care across the health system, endoscopy reports and follow-up recommendations are provided to patients by the performing gastroenterologist, and patients completing FIT are also be notified of their results. If a FIT positive patient does not schedule diagnostic colonoscopy follow-up within two months of their result and has not received standard follow-up outreach from the practice, the research team sends a note in the EHR to population health coordinators who will provide additional support.

We will obtain baseline data from the EHR on demographics, prior CRC screening, co-morbidities, and mortality risk from automated data extraction and free text searches, as needed. We will use chart review to track outcomes of colonoscopies that are performed with polypectomy, so that we can categorize the finding. Study data are being collected and managed using REDCap electronic data capture tools hosted at the University of Pennsylvania. [37,38]

Changes in Health Maintenance (HM) status are assessed via daily Clarity query to identify documentation of screening results and determine continued outreach. All HM status changes and results (internal or external) picked up by this query are chart-reviewed and only counted toward an outcome if documentation is present in the patient chart.

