For Aim 2 (visit-based nudge comparison), we will again fit a generalized linear model (GLM) for the binomial family with a logit link, robust standard errors, fixed effect for clinic, and study arm at stage 1 (no outreach, colonoscopy outreach, sequential choice outreach) and stage 2 (nudge, no nudge) to compare visit-based nudges to usual care for the primary outcome. Individuals who attended at least 1 PCP visit will be included in this analysis. As a sensitivity analysis we may consider the potential interaction between the terms for the arm at stage 1 and at stage 2. This will allow us to evaluate the effect of visit-based nudges in the context of colonoscopy and sequential choice outreach. We will perform a similar analysis for the detection of adenomas, sessile serrated polyps or advanced adenomas and a zero-inflated Poisson regression model with robust standard errors for the proportion of time screened (days). We will also include socioeconomic and clinical variables in an exploratory multivariable model, including age, sex, race, insurance type, income (zip code level), and prior CRC screening, along with interaction terms with the patient outreach choice assignment. We will also conduct a sensitivity analysis to examine whether those that showed up for a visit in each arm are similar to those that were originally randomized to that nudge arm, and conduct a reweighted analysis in order to be representative of those originally randomized. We will perform a subgroup analysis of Black patients for each of the primary comparisons and conduct additional subgroup analyses for non-rare subgroups in an exploratory fashion, including the same socioeconomic and clinical variables described above for all.

To evaluate the performance of the 3-year mortality index algorithm, we will perform a 3-year descriptive retrospective evaluation of CRC ordering rates, CRC screening completion rates, number of emergency department visits, number of hospitalizations, and mortality among all patients excluded from participation by the mortality index algorithm.

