## Discussion

4.

Durably increasing CRC screening rates equitably among primary care patients requires interventions at multiple levels. By addressing gaps that have been identified from prior research, this trial leverages existing screening infrastructure and layers it with an organized approach, novel use of existing EHR functionality, informed by key concepts from the field of behavioral science.

This will be the first large, prospective trial evaluating the long-term effectiveness of offering sequential choice of colonoscopy then FIT compared to colonoscopy through a multi-level, centralized outreach and visit-based nudge design. Importantly, there is a pre-specified subgroup analysis of Black patients, who are known to have disparities in access and outcomes for CRC. Additionally, if validated, the mortality algorithm could be helpful for the identification of an eligible population without the need for extensive chart review. Further, we have designed and embedded this trial in partnership with health system leadership in a pragmatic design, and have integrated many aspects of the intervention in the EHR and with routine care to make it more efficient and adaptable to other clinical settings.

There are some limitations. While the health system includes a diverse range of primary care practices across the Philadelphia region, the learnings may not translate to other regions or types of health systems. We are not powered to detect differences in clinical outcomes such as cancer incidence and mortality, and we may not be able to fully capture care that happens outside of our health system, despite the integrated EHR and access to some data from other health systems.

In conclusion, this study will provide additional evidence on operationalizing population-level screening programs to reduce CRC burden, and inform future interventions to increase CRC screening.

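### The planned evaluation of the 3-year mortality index follows only the patients it excluded, so it can give PPV and a description of them but not sensitivity, specificity, NPV, accuracy or full-range AUC

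*Protocol article*

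**What the plan says.** The last paragraph of section 3.3 (Analytic plan) states a purpose and a method together: "To evaluate the performance of the 3-year mortality index algorithm, we will perform a 3-year descriptive retrospective evaluation". The outcomes are CRC test ordering, screening completion, emergency visits, "number of hospitalizations, and mortality among all patients excluded from participation by the mortality index algorithm". No group that the index left in is named.

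Section 2.2 (Eligibility and enrollment) says the model was "trained on a cohort of 42,451 patients eligible for CRC screening", of whom 779 (1.8%) died within 3 years. It reports a held-out AUC of 0.844 and, at a threshold of 0.9, accuracy of 97.2% and PPV of 26.8%. At enrolment, "625 patients of 19,969 eligible patients (3.1 %) were excluded because of an increased risk for mortality within three years".

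The remaining patients are the trial population: "Upon completion of enrollment, 19,344 patients were randomized as follows" (section 2.3). Section 2.4 says of data collection: "We will obtain baseline data from the EHR on demographics, prior CRC screening, co-morbidities, and mortality risk". Sections 3.2 and 3.3 treat death in randomised patients as failure to be screened. The Discussion adds that, "if validated, the mortality algorithm could be helpful for the identification of an eligible population without the need for extensive chart review".

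**The concern.** The purpose is wider than the population can support. A group made up wholly of index-positive patients contains true positives and false positives and nothing else. Deaths among patients whom the index passed as low risk, and survivors it classified correctly, lie outside the data. Of the usual threshold measures, only PPV can be estimated.

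The screening, emergency and hospitalisation rates raise a second problem. With no unflagged group beside them, they cannot show whether excluded patients differ from those kept in.

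What is at stake is the secondary claim about the index. Anyone considering it as an eligibility tool would want to know how many deaths it misses and whether its development discrimination held up in the enrolled population. The planned data answer neither question. This is not detail deferred to a fuller plan, because the article itself fixes both the purpose and the restricted population.

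**Working it through.** **Reproducing the stated counts (sections 2.2 and 2.3)**

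- Development deaths: 779/42,451 = 1.84% (stated 1.8%).
- Excluded at enrolment: 625/19,969 = 3.13% (stated 3.1%).
- Not excluded: 19,969 − 625 = 19,344. This equals the randomised total, and the five arms add up to it: 3877 + 3865 + 3870 + 3867 + 3865 = 19,344.

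The randomised cohort is therefore exactly the complement of the excluded group.

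**What the development figures imply**

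Let p be mortality, A accuracy, V the PPV and f the share flagged. The errors are the false positives, f(1 − V), plus the missed deaths, p − fV. So 1 − A = f(1 − V) + p − fV, which gives

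- f = (1 − p − A)/(1 − 2V)
- sensitivity = fV/p

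The article gives no mortality for the held-out test set, so p is an assumption. With A = 0.972 and V = 0.268, the denominator is 1 − 0.536 = 0.464.

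| Assumed test-set mortality | Share flagged | Implied sensitivity |
|---|---|---|
| 1.6% | 0.012/0.464 = 2.6% | 0.268 × 0.0259/0.016 = 43% |
| 1.84% (whole cohort) | 0.00965/0.464 = 2.1% | 0.268 × 0.0208/0.01835 = 30% |
| 2.0% | 0.008/0.464 = 1.7% | 0.268 × 0.0172/0.020 = 23% |

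At mortality of 1.8% to 1.84%, rounding in the stated accuracy and PPV moves the 30% only between about 29% and 34%. Across the whole table the index misses more than half of the deaths.

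**What the planned evaluation would and would not show**

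Suppose the stated PPV carries over: 625 × 0.268 gives about 168 deaths among the excluded. PPV is then 168/625 = 26.9%, with an exact 95% interval of 23.4% to 30.5%. That is a usefully precise estimate. Sensitivity, 168/(168 + deaths among the 19,344), depends on a figure that the planned evaluation does not use:

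| Assumed 3-year mortality in the 19,344 | Deaths | Sensitivity | NPV |
|---|---|---|---|
| 0.25% | 48 | 78% | 99.75% |
| 0.5% | 97 | 63% | 99.5% |
| 1.03% (total mortality as in development) | 199 | 46% | 98.97% |
| 1.8% | 348 | 33% | 98.2% |
| 2.5% | 484 | 26% | 97.5% |

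The planned data are identical in all five rows.

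**Share flagged at enrolment**

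The central implied share, 2.08%, would flag about 415 of 19,969, against 625 observed: a ratio of 3.13/2.08 = 1.5. Over the assumed mortality range the ratio runs from 3.13/2.59 = 1.2 to 3.13/1.72 = 1.8. Whether that reflects a change in case mix or in the model's behaviour cannot be settled from the 625 alone.

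**The case against.** The best defence is that the planned analysis matches what the index was built for. Section 2.2 explains that it was designed so as not to exclude under-represented patients who could still benefit from screening. The key error for that purpose is the false positive, and following every excluded patient measures it directly: how many survived, were ordered a test, completed screening or needed acute care. This stands. A reader might infer that the evaluation says nothing about whether the index performs, and the documents do not support that. PPV and the outcomes of excluded patients are a real, if partial, evaluation, and ranking among scores above 0.9 could also be examined.

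A reader might also infer that the Discussion's condition about validation rests on this analysis. The article does not say so. It calls the analysis descriptive and retrospective, and a held-out internal validation is already reported in section 2.2.

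Two further cautions stand. The implied sensitivity is derived, not reported, and depends on an unstated test-set mortality; the higher share flagged at enrolment is likewise not established as a shift. Low sensitivity, and the fact that calling everyone a survivor would be 98.2% accurate (100% − 1.84%) against the stated 97.2%, concern the development model and its threshold. They are not errors in the planned analysis. They show only why missed deaths are worth measuring.

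It can also be said that this is an ancillary analysis, that no trial conclusion depends on it, and that the complementary analysis stays available later. That limits the importance of the point but does not remove the mismatch, which lies in what the article states.

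**Conclusion.** The point holds in limited form. Section 3.3 promises an evaluation of performance but names a population that yields PPV and a description of the excluded. Sensitivity, specificity, NPV, accuracy and full-range AUC are out of reach, so the development AUC of 0.844 and accuracy of 97.2% would go unchecked in the enrolled population. The screening and utilisation rates would stand without a comparator.

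The size of the gap is shown by the implied development sensitivity: about 30% if test-set mortality equalled the cohort's 1.84%, and about 43% to 23% for 1.6% to 2.0%. With the PPV carried over, sensitivity at enrolment could be anywhere from 78% to 26% over the assumed mortality range for unflagged patients, and the planned data could not tell these apart.

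The consequence is confined to claims about the index. No primary or secondary trial comparison is affected.

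**What to change.** Evaluate 3-year mortality by index score in all 19,969 scored patients, the 625 excluded and the 19,344 randomised together. Report AUC, and sensitivity, specificity, PPV and NPV at the 0.9 threshold. Ascertain deaths from the same source and over the same 3-year window in both groups.

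Report calibration only after allowing for the weighted fit. A cut-off of 0.9 that goes with a PPV of 26.8% shows that the raw score is not a calibrated probability.

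Compare ordering, screening completion, emergency visits and hospitalisations in the excluded patients with arm 1, which receives no outreach or nudge from the trial.

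If this is not wanted, relabel the analysis as a description of excluded patients with an estimate of PPV.

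The cost is one extra analysis and no new patients or procedures. It assumes that the baseline mortality risk listed in section 2.4 includes the stored score, and that deaths in randomised patients are recorded as sections 3.2 and 3.3 indicate. There is time to make the change, since the trial runs to January 2027 and analysis follows completion of the 3-year period.

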### Mixed methods analysis

3.4.

The annual embedded survey consists of 16 individual items spanning five psychosocial constructs: 1) salience and coherence, 2) social influence, 3) cancer worries, 4) perceived susceptibility, and 5) response efficacy. [39,40] Each construct can be summed to create a score within each construct, and in total related to beliefs about CRC screening. We will calculate mean differences within each of the five constructs, evaluate each construct on its own scale, and overall look for any associations between CRC screening completion at 3 years and screening beliefs. Finally, we’ll compare screening exposure and preference responses to the type of screening completed at 3 years, if any. We will compare outcomes for those offered the survey and those who were not, to see if receiving the survey was associated with cancer screening completion.

For analysis of the qualitative interview transcripts, two members of the research team will independently review the transcripts for inductive themes through an iterative process using the constant comparative approach. [44–46] After the study team reviews five sets of transcripts, we will develop a coding scheme that will be applied to subsequent data and modified as the study progresses and new themes emerge. The study team members will assess and reassess our inter-rater reliability.

Finally, we will perform a cost analysis using resource utilization to determine the incremental cost of outreach in each arm and the incremental cost of additional patients screened to evaluate resource requirements for scale. We will evaluate the cost from the perspective of the health system, including the time spent by staff that would be needed as part of routine operations when implemented, while not including effort for activities that are only part of the research process.

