### Mixed methods evaluation

2.5.

Annually, upon completion of all direct outreach in Batch 3, we send a validated survey guided by the Preventive Health Model (PHM), a selfregulation model shown to predict colorectal screening behaviors in a diverse population, to a select group of enrolled participants. [39,40] The original survey was developed and refined by Vernon and colleagues in 1997 and further validated in a larger and more diverse population by Tiro and colleagues in 2005. [40,41] For a target sample size of 100 completed surveys per year (300 total), and assuming a 20 % response rate, we are randomly selecting a minimum of 500 patients each year, stratified by race (Black patients vs all others) and study arms (intervention arms only) to complete the survey.

The survey consists of 16 individual items spanning five psychosocial constructs: 1) salience and coherence, 2) social influence, 3) cancer worries, 4) perceived susceptibility, and 5) response efficacy. It will also include questions about CRC screening exposure and preferences. Patients randomly selected to complete the survey receive an invite via text message (Way to Health), and participants receive up to 2 automated reminders at 4 and 9 days. If our sample is lower than expected, remaining participants are purposively selected in batches of 10 to receive a manually generated text message offering a scheduled date and time to complete the survey by phone until an appropriate sample is obtained. Survey administration is repeated in Years 2 and 3, with no repeated participants in subsequent years. We monitor responses by study arm, race, and sex to ensure a representative sample.

In year 3 of the trial, a purposive sample of 60 patients will be contacted by phone to conduct qualitative interviews to understand their experience with the specific outreach strategy and the reasons for the effectiveness (or lack of effectiveness) of each intervention. Guided by domains with the PHM, we will also ask semi-structured questions about their perception of the impact and design of outreach.

We will also conduct qualitative interviews with 15 clinicians in the visit-based nudge arms to better understand their experiences with the interventions. Interview participants (patients and clinicians) will be consented and given a $25 gift card in appreciation of their time.

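### The planned check for a survey effect does not limit its comparator to the outreach arms, so read literally it mixes the survey with the outreach itself

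*Protocol article*

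**What the plan says.** Under Mixed methods evaluation (2.5), the survey draw is "stratified by race (Black patients vs all others) and study arms (intervention arms only) to complete the survey". On its size, the article says "we are randomly selecting a minimum of 500 patients each year", over three years. Contact is by text: those drawn "receive an invite via text message (Way to Health), and participants receive up to 2 automated reminders at 4 and 9 days". If too few respond, "remaining participants are purposively selected in batches of 10 to receive a manually generated text message" offering a phone appointment. On repeat sampling: "Survey administration is repeated in Years 2 and 3, with no repeated participants in subsequent years".

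Under Mixed methods analysis (3.4), the check on the survey's own effect is a single sentence: "We will compare outcomes for those offered the survey and those who were not, to see if receiving the survey was associated" with screening completion. It names no arms, strata or adjustment for the second group.

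Under Interventions (2.4), arm 1 receives neither outreach nor nudges from the trial.

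**The concern.** A patient can be offered the survey only if randomized to an outreach arm. Being offered it is therefore tied to the randomized intervention. A comparison of everyone offered with everyone not offered sets a group made up wholly of outreach patients against a mixture of outreach and no-outreach patients. If outreach works as planned, the offered group will look better even when the survey does nothing.

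This is the only check on survey reactivity that the article states. A falsely positive result would credit the survey with part of the outreach effect. Because only the outreach arms were surveyed, it would also cast needless doubt on the comparisons with arm 1. The remedy is already in the design: within the strata the draw is random, so a near-unbiased comparison is available.

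**Working it through.** **Inputs**
- Randomized (2.3): arm 1 3,877; arms 2a, 2b, 3a and 3b 3,865, 3,870, 3,867 and 3,865.
- Planning rates (3.2): 27% in arm 1, 30% in arm 2, 33% in arm 3. The article itself uses their average, 31.5%, for the outreach arms.
- Survey (2.5): 100 completed per year at 20% response.

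**1. The plan's own figures**
- Invitations: 100 / 0.20 = 500 per year, as stated. Over three years this is 1,500 different patients, if the no-repeat rule covers everyone invited. It is a floor, because 500 is a minimum.
- Power, by normal approximation with pooled variance at two-sided 0.017: 27% v 30% with 4,000 v 8,000 gives 85.1% (stated 85%); 30% v 33% with 8,000 v 8,000 gives 95.5% (stated 96%). The planning rates are therefore being read as the article intends.

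**2. Who is in the comparator if it is taken literally**
- Outreach patients: 3,865 + 3,870 + 3,867 + 3,865 = 15,467.
- Not drawn: 15,467 - 1,500 = 13,967.
- Everyone not offered: 13,967 + 3,877 = 17,844. Arm 1 share: 3,877 / 17,844 = 21.7%.

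**3. Expected difference with no survey effect**
- Offered: 31.5%, taking the draw as even across arms 2 and 3.
- Not offered: (3,877 x 0.27 + 13,967 x 0.315) / 17,844 = 30.5%.
- Difference: arm 1 share x (outreach rate - arm 1 rate) = 0.217 x 4.5 = +0.98 point.
- Range: 0.217 x 3 = +0.65 if both outreach arms are at 30%; 0.217 x 6 = +1.30 if both are at 33%.

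**4. How often a 5% test would reject**
- SE = sqrt(0.315 x 0.685 / 1,500 + 0.305 x 0.695 / 17,844) = 1.25 points.
- z shift = 0.98 / 1.25 = 0.78.
- Rejection = 1 - Φ(1.96 - 0.78) + Φ(-1.96 - 0.78) = about 12%. Over the range in step 3 it is 8% to 18%.

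**5. The same check within arms 2 and 3**
- Expected null difference due to arm 1: 31.5 - 31.5 = 0.
- SE = sqrt(0.315 x 0.685 x (1 / 1,500 + 1 / 13,967)) = 1.26 points. Dropping arm 1 costs almost no precision, because the 1,500 drawn patients dominate the variance.

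**6. Why the strata also matter, though less**
- Black patients in arms 2 and 3 (Table 1): (1,232 + 1,223 + 1,241 + 1,176) / 15,467 = 4,872 / 15,467 = 31.5%.
- Suppose half of those drawn are Black (assumption; the article gives no split): 750 of 1,500. Among the undrawn, the share is (4,872 - 750) / 13,967 = 29.5%.
- With the article's 30.9% for Black outreach patients and 31.5% overall, the implied rate for others is (31.5 - 0.315 x 30.9) / 0.685 = 31.8%.
- Unadjusted imbalance: (0.500 - 0.295) x (30.9 - 31.8) = about -0.2 point.

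**7. Carry-over of the survey into the outreach v no-outreach contrasts**
- Share invited: 1,500 / 15,467 = 9.7%, against none in arm 1.
- The documents give no survey effect. Assumed effects among those invited of 1, 3 and 5 points add 0.10, 0.29 and 0.48 point to a contrast planned at 3 points.

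**The case against.** The strongest reply is that the article never says arm 1 is in the comparator. The sampling frame was limited to the intervention arms one section earlier, so a sympathetic reader may take the check as drawn v undrawn within that frame, which is a randomized comparison. The article is also condensed, and details of an ancillary analysis usually sit in a fuller document.

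The first part stands. A reader might infer that the plan puts arm 1 in the comparator; the text supports only that it fails to exclude it. The second part does not dispose of the point. The article states the comparison and its purpose, and an analyst who follows that sentence as written gets a contrast that cannot serve the purpose.

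Four further limits also stand.
- A reader might infer that the check would generally show a false survey effect. At about 12% rejection, it would show nothing significant in roughly 88% of cases.
- Screening completed before the invitation does not bias a random draw. It balances within strata and only dilutes a real effect.
- Surveying only the outreach arms is a design choice, not an error. It keeps arm 1 free of trial contact.
- A reader might infer that the survey materially inflates the comparisons with arm 1. The documents give no survey effect, and the patients drawn already receive orders, letters and texts under outreach. Large assumed effects are hard to credit when the whole programme is planned at 3 points (arm 2) to 6 points (arm 3) over arm 1.

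**Conclusion.** The point holds as a wording defect in a stated, ancillary analysis, and its severity is minor. Taken literally, the comparison carries a bias of about +1.0 point (range +0.65 to +1.30) and a false-positive rate of about 12% (8% to 18%) instead of 5%. This rests on the plan's own completion rates, the minimum of 1,500 invitations to different patients, a draw even across arms 2 and 3, and arm 1 being left in the comparator.

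The primary contrasts are probably little affected: 0.1 to 0.3 point for an assumed survey effect of 1 to 3 points. If the draw is even across the outreach arms, sequential choice v colonoscopy only and nudge v no nudge are largely untouched. The documents do not support calling the primary results confounded by the survey.

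**What to change.** In Mixed methods analysis (3.4), state that the check compares randomly drawn with undrawn patients within arms 2 and 3 only, in each year's sampling frame, adjusted for the sampling strata (race group and arm). Handle patients added purposively separately, since they were not selected at random. This changes wording only and costs almost no precision (SE 1.26 v 1.25 points). It does need a record of who was drawn, when, and in which stratum.

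Two additions are optional:
- Count only completions after the invitation date, using the same calendar date for undrawn patients and including only those not yet screened on it. This reduces dilution; it does not correct a bias.
- Report arm 2 v arm 1 and arm 3 v arm 1 without the drawn patients, with the remaining outreach patients reweighted by stratum, as a sensitivity analysis. The cost is about 10% fewer outreach patients in that analysis.
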